**If blood ketones levels are:**

**Between 0.0 and 0.6 mmol/L**, instruct participant to:

- Drink sugar-free and caffeine-free fluids.
- Check the cartridge, catheter and insertion site.
- Avoid skipping meal and have a minimal amount of carbohydrate (> 30g) in such meal.
- Use the iMAP or participant personal insulin pump to calculate a correction bolus. Administer correction bolus via the pump.
- Monitor signs and symptoms of hyperglycemia (excessive thirst, urination, abdominal pain, nausea, weakness, etc...) and ketones.
- Monitor blood glucose and ketone levels 2 hours after correction bolus is administered.
- If hyperglycemia persists (> 16 mmol/L) and/or blood ketone levels increase 2 hours post correction, change infusion set and follow ketone management procedure.

**Between 0.6 and 1.5 mmol/L**, instruct participant to:

- Contact their study nurse
- Drink sugar-free and caffeine-free fluids (aim 200-250 ml every 30-60 minutes)
- Use bolus calculator on insulin pump or iMAP to calculate correction bolus. Administer the bolus via syringe or insulin pen. (If on CLS, the participant should disconnect the study pump from their body and deliver the same bolus through the system, so it accounts for the insulin given via the syringe, and proper IOB is calculated)

*\*Participant should be encouraged to eat a small amount of carbs (15-45g), there should be a bolus administered for any carb intake.*

- Change the pump cartridge, tubing and infusion set.
- Verify if cannula seems kinked or blocked, and if there is blood at the old insertion site. Check if their insulin was properly stored (as per supplier recommendations). This information should be charted in participant file by the study nurse.
- Monitor signs and symptoms of hyperglycemia (excessive thirst, urination, abdominal pain, nausea, weakness, etc...) and ketones
- Monitor blood glucose and blood ketones levels 2 hours after correction bolus is administered
- If hyperglycemia persists or blood ketone levels remain positive (one or both values have not decreased from initial values), notify study physician and keep supporting participant by following the ketone management procedure.

**Above 1.5 mmol/L**, instruct participant to:

- Contact their study nurse (study physician should be notified immediately for ketone values above 3.0 mmol/L).
- Drink sugar-free and caffeine-free fluids (aim at 200-250 ml every 30-60 minutes)

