- Use bolus calculator on insulin pump or iMAP to calculate correction bolus. Multiply **correction bolus** by 1.5. (Ex correction bolus recommendation = 2U, Multiply by 1.5 = 3U). Administer the bolus via syringe or insulin pen. If on CLS, the participant should disconnect the study pump from their body and deliver the same bolus through the system, so it accounts for the insulin given via the syringe, and proper IOB (insulin on board) is calculated.
- *\*Participant should be encouraged to eat a small amount of carbs (15-45g), there should be a bolus administered for any carb intake. It's important that only the correction part of the bolus is multiplied.*
- Change the cartridge, tubing and infusion set.
- Verify if cannula seems kinked or blocked, and if there is blood at the old insertion site. Check if their insulin was properly stored (as per supplier recommendations). This information should be charted in participant file by the study nurse.

- Monitor signs and symptoms of hyperglycemia (excessive thirst, urination, abdominal pain, nausea, weakness, etc...) and ketones
- Monitor blood glucose and blood ketones levels 2 hours after correction bolus is administered
- If hyperglycemia persists or blood ketone levels remain positive (one or both values have not decreased from initial values), notify study physician and keep supporting participant by following the ketone management procedure.

In the event of positive blood ketones (above 0,6 mmol/L), the participant will only return to pump or iMAP pump therapy once ketones are below 0,6 mmol/L.

Participants will record all blood ketone levels measured and infusion set changes in the Study Participant Journal. The reasons for infusion set changes are documented in the journal (ex: planned vs unplanned).

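### Annex A's return-to-pump rule, read literally, leaves a participant with raised ketones on injected boluses with no stated basal insulin, and it conflicts with the annex's own set-change step

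*Protocol*

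**What the plan says.** Annex A sorts the response by blood ketone level. Below 0.6 mmol/L the correction bolus is given through the pump. In the two positive bands (0.6 to 1.5 mmol/L and above 1.5 mmol/L) the instruction changes to "Administer the bolus via syringe or insulin pen". On CLS, "the participant should disconnect the study pump from their body and deliver the same bolus through the system", so that the system counts the injected insulin. A small carbohydrate intake is encouraged in both bands, and "there should be a bolus administered for any carb intake".

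Both positive bands then order new hardware: "Change the pump cartridge, tubing and infusion set" in the lower band and "Change the cartridge, tubing and infusion set" in the upper. The follow-up is the same in both: "Monitor blood glucose and blood ketones levels 2 hours after correction bolus is administered".

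After the bands comes one closing rule for any value above 0.6 mmol/L: "the participant will only return to pump or iMAP pump therapy once ketones are below 0,6 mmol/L". It names both the ordinary pump and the iMAP. I take the iMAP to be the study closed-loop system, because Annex A sets it against the participant's personal pump.

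**The concern.** The closing rule speaks of a return to pump therapy, which presupposes that the participant is off the pump. If so, the only insulin the annex names for that interval is the correction bolus and any carbohydrate bolus. A person with type 1 diabetes on a pump gets basal insulin from the pump. A participant or nurse who applies the sentence as written would therefore hold back basal delivery while ketones are raised, when the purpose of the procedure is to restore insulin.

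What is at stake is participant safety during ketosis. The statistical plan is not affected.

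**Working it through.** The plan states no figure here that could be recomputed, so the check sets the texts side by side.

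1. **Who is covered.** The trigger is ketones above 0.6 mmol/L, which takes in both positive bands. Because the rule names both kinds of pump, it reaches both interventions; under SAPT participants use their own pump (Section 7.2.2).

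2. **What puts the participant off the pump.** On CLS there are two sources: the disconnect step in each positive band and the closing rule. On SAPT no step says to disconnect, so the closing rule is the only source.

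3. **What puts the participant back on.** No step in Annex A says to reattach the pump or resume delivery. The nearest is the change of cartridge, tubing and infusion set, which makes little sense unless the new set is to be used. The closing rule instead makes the return wait for ketones below 0.6 mmol/L.

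4. **What insulin is stated meanwhile.** The annex gives the correction bolus (multiplied by 1.5 above 1.5 mmol/L, as in "Ex correction bolus recommendation = 2U, Multiply by 1.5 = 3U") and a bolus for carbohydrate. It does not mention basal insulin. The measures listed under hyperglycemia in Section 3.4 (correction bolus, hydration, set or reservoir change, syringe or pen bolus) do not mention it either.

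5. **What limits the exposure.**
   - The study nurse is contacted in both positive bands.
   - The study physician is notified if values have not fallen at the 2-hour recheck, and at once above 3.0 mmol/L.
   - Section 3.2 provides a ketone meter, catheters and syringes.
   - Section 3.4 asks for regular contact with the team and ends the intervention if the situation is unresolved at 6 hours.
   - Section 3.5 gives 24/7 support.

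   Each shortens or supervises the interval. None says how basal need is met.

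6. **The two readings.** Literally, basal delivery stops until a recheck shows ketones below 0.6 mmol/L. By inference from the set change, the pump restarts on the new set at once, and the closing sentence contradicts that. The text does not say which is meant.

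**The case against.** The best defence is that the closing sentence is loose, not wrong. Corrections go through the pump below 0.6 mmol/L and by syringe or pen above it, so a return to pump therapy could mean a return to pump-delivered corrections. The disconnect step has one stated purpose, logging the injected bolus so that insulin on board is right, and that matters mostly if the system will dose again soon. The routine catheter change every 2 to 3 days in Section 2 carries no reconnect step either, and nobody would read it as leaving the pump off. The steps are also given by staff, with mandatory nurse contact.

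Much of this stands: restarting on the new set is the likely intent. But the sentence says pump therapy, not corrections, and no other section supplies a basal rule that would override it. The conflict remains for whoever has to apply the text.

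A reader might infer more than the documents support:

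- **A shortfall in units.** The protocol gives no basal rate. The multiplier example is arithmetic for a correction dose and is not described as basal cover, so it cannot be used to work out a net deficit.
- **No backup insulin.** Section 2 lists only Aspart and Lispro. But Section 3.4 promises a glucagon kit that Section 2 does not list, so that list is not a full inventory of rescue supplies.
- **No time limit between 0.6 and 1.5 mmol/L.** The 6-hour stop follows a sentence about values above 1.5 mmol/L, but it refers to the situation in general and can be read to cover both bands.

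**Conclusion.** The point holds as a conflict within a safety procedure. One sentence, followed literally, withholds basal insulin from a pump-treated participant with raised ketones; the set-change step beside it implies the opposite. It applies more strongly to CLS, where a disconnect step is also written, than to SAPT.

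The size is one sentence, reaching both positive ketone bands. The first scheduled recheck is at 2 hours and the stop in Section 3.4 is at 6 hours, so supervised exposure is bounded if that stop is read as covering both bands. The finding is that the annex lacks a stated basal rule and contradicts itself. It does not establish that any participant would in fact go without basal insulin, since staff are involved and the likely intent is to restart. No bias in time in range or any other endpoint follows from the documents.

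This should be fixed, because the risk is clinical and the remedy is short. The wording is certain; the authors' intent and how staff would act are not.

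**What to change.** Amend the closing sentence of Annex A for both interventions. After the injected correction bolus and the change of cartridge, tubing and infusion set, the participant reconnects the pump on the new set and resumes basal delivery at once. Correction boluses continue by syringe or pen until ketones are below 0.6 mmol/L.

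The clinical team should also state whether closed-loop dosing or the usual basal rate in open loop runs in that interval. Section 3.3 shows that the CLS can already run the usual basal rate in open loop after a lost connection, so either looks feasible.

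If the team does want the pump off until ketones clear, Annex A should say so plainly and state the injected insulin that covers basal need.

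The cost is a short amendment and revised participant instructions. The downside is that, if the new set also fails, basal insulin is again undelivered until the 2-hour recheck already in the annex. Sample size, visits, endpoints and analysis stay as they are.

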## Reporting

All positive blood ketones events ( $> 0.6$  mmol/L) will be documented as Adverse Events (AE) in the participant chart. Should the local ERB require submission for this type of event, AE will be submitted to ERB for review. Should the AE be classified as serious by study physician (hospitalization required, etc...), the event will be documented as SAE and will be reported to ERB, DSMB and regulatory authorities.
